#### Economic Evaluation

The economic analysis will take a health and social care perspective. Service use will be combined with appropriate unit costs (eg, from Kent University and NHS Reference Costs) to generate service costs. QALYs gained over the period from baseline to 12-week follow-up will be generated using area-under-the-curve methods from the EQ-5D (using published tariffs from the University of York) combined with costs in the cost-effectiveness analysis. If the intervention group has lower costs and better outcomes than the control group, then the intervention will be seen as “dominant.” If the intervention group has higher costs and better outcomes, we will use incremental cost-effectiveness ratios to identify the extra cost incurred to achieve one extra QALY. Uncertainty around cost-effectiveness estimates will be explored using cost-effectiveness planes (produced from outcome-cost combinations from 1000 bootstrapped resamples). Interpretation will be aided using cost-effectiveness acceptability curves derived using the net-benefit approach with values between £0 and £100,000, placed on a QALY gain so as to include the threshold used by NICE (2007) [7]. We will also conduct similar analyses using costs and the primary outcome measure. However, QALYs are the main measure for the economic evaluation given that thresholds for cost-effectiveness used by NICE exist.

#### 12-Week Follow-Up

The main outcomes, including QALYs, will be measured over the 12-week period from baseline assessment to follow-up. We would expect to see a change in the EQ-5D (which provides us with QALY information) and the WSAS over this time. We will also measure the intervention costs and any short-term impact on the use of other services through the CSRI. We recognize that longer-term impacts, which we are unable to measure may also be important. We will measure serious deterioration using a composite measure including the CGI (“much” or “very much worse”), those who actively withdraw from their intervention, or those whose SF-36 PF score falls by 10 or more points.

#### 12-Month Follow-Up

We will go on to measure how many appointments each participant has with an SMC doctor and with a therapist (and which therapist: psychologist, physiotherapist, occupational therapist, or group therapy) after their trial participation up to 12 months from randomization. We will estimate the costs of the interventions and compare between the groups.

### Data Protection

Participants will be allocated a unique 8-digit identification number made up of a center number, an individual patient number, and patient initials. This number is assigned to the patient and is used on assessment forms prior to transfer of data, so that they are anonymized at source. A list of names and corresponding identification numbers will be kept separately and securely on an encrypted university server. All guided support sessions will be audio-recorded if consent is given, and they will be stored on an encrypted university server.

### Data Monitoring

The DMEC will receive notice of SAEs and SARs for the sample as a whole and per treatment arm. If the incidence of SAEs of a similar type are greater than would be expected in this population, the DMEC will be able to retrieve data according to trial arm, to determine any evidence of excess in either arm. NSAEs will be included in the safety reporting of the completed trial. Suspected unexpected serious adverse reactions (SUSARs) will be reported separately.

### Independent Scrutiny

At the end of the trial, two independent scrutineers will be appointed to consider whether any AE is an SAE and whether any SAE is an SAR. These figures will be reported.

### Compliance

The trial will be conducted in compliance with the Declaration of Helsinki, the trial protocol, Medical Research Council Good Clinical Practice (GCP) guidance, the Data Protection Act (1998), the Multi-centre Research Ethics Committee (MREC), and Local Research Ethics Committees (LREC) approvals and other regulatory requirements, as appropriate. The final trial publication will include all items recommended under CONSORT [49].

### Qualitative Study

#### Purpose

We will undertake a nested qualitative study with a subsample of participants to ascertain patients’ views and experiences of GES, specifically looking for differences in perceptions and experiences between those who improved and worsened with GES.

Both our patient representatives and the TSC suggested using the trial to better understand why patients vary in their responses to graded exercise therapy (GET), particularly by examining engagement and other barriers/facilitators to successful treatment. The best way to gather this knowledge is to undertake a small qualitative study, stratified by both good and poor outcomes. We will conduct one-on-one interviews with participants who have taken part in the active arm of the trial to investigate variations in participant attitudes to, and experiences of, GES. This study will be nested within the time-frame for the main trial.

#### Background Issues

A recent meta-synthesis of qualitative studies uncovered various ways in which people with CFS/ME interpret and experience their illness and their treatments [50]. Themes included wide variability in symptoms, amount of perceived control, and theories about causation and best coping strategies (eg, reducing activities, listening to the body, and balancing activities). Perspectives of patients are also known to change with treatment experience. For instance, if beliefs about the need to avoid exercise and less helpful thought patterns can be addressed (eg, catastrophic thinking), then improvements in fatigue may follow [51]. At the same time, some patient organizations believe that one particular treatment, graded exercise therapy (GET), is harmful to CFS/ME patients [12]. Qualitative research can provide a deeper understanding of the way that participants approach, experience, and give meaning to interventions like GES [52]. There is no published, qualitative research that investigates variation in participant attitudes to, and experiences of, GET in a randomized controlled trial. Yet, the evidence is that patients who benefit from such interventions are likely to approach the intervention differently than those who do not [53]. Our preliminary (unpublished) analysis of free-text feedback from GET participants in the PACE trial [11] suggested different categories of participants. For instance, people differed in their appraisals of GET from positive to negative, and whether they attended more to the learning, support, treatment, and/or contextual issues outside of the trial. However, we do not yet have sufficient data to examine the significance of different styles of patient engagement with GET.

#### Research Questions for the Qualitative Study

The following two research questions will be investigated in the qualitative study: (1) Are there any differences in treatment perceptions and experiences between those trial participants who improved and those who worsened during use of guided self-help based on GET? and (2) What are the implications for the way patients understand “getting better?”

#### Recruitment and Sampling Strategy

We aim to recruit up to 20 participants, all of whom will have received GES. Participants will be stratified into 2 similar-sized groups of either improvement or deterioration (CGI score at 12-week follow-up assessment of “much” or “very much” better versus “much,” or “very much” worse) for comparison [39]. We will seek written informed consent from these 20 participants. Participants will have completed the 12-week follow-up assessment, and will be recruited at least one month later to allow time for them to reflect on their GES and trial experience.

#### Participant Involvement

Participants will undertake a one-off semistructured interview, either face-to-face, by telephone, or by Skype™, depending on their preference.

#### Data Collection

Qualitative semistructured interviews, digital audio-recorded, with fully informed consent, will be conducted with participants. An experienced qualitative researcher will conduct the interviews, using a semistructured approach [54]. By ensuring the same topics are covered in each interview, we will collect comparable data about participants’ experiences of the trial and treatment within each group. In addition, the semistructured approach will allow greater flexibility for participants to highlight their specific concerns, meanings, and priorities, even if not anticipated by the researchers. Topics will include before and after trial well-being, expectations of treatment, understanding of “baseline” and “recovery,” the meaning of exercise, barriers and facilitators to treatment, and any outside influences on trial participation. Thus, we will use an approach suited to collecting a wide range of experiences in each group. We will use face-to-face interviews to collect people’s experiences (eg, in people’s homes, or a university interview room). We will also use less conventional ways to include the perspectives of people who may have trouble participating; for example, recording of interviews over the phone, or the use of Skype™ video calls for interviews. Sample questions are provided in Multimedia Appendix 1.

#### Data Management and Analysis

The audio-recordings from the interviews will be professionally transcribed (a confidentiality agreement will be in place). The transcription will be reviewed against the audio by the researcher for errors and to remove any identifying information, and then returned to the participant to check accuracy and add any clarifying points at the end of the interview, with a deadline of one month to reply.

Thematic analysis (ie, “identifying, analyzing, and reporting patterns within data”) is a basic building block of all kinds of qualitative analysis [55], and will be the approach used for analysis in this study. Data will be inputted and coded in the qualitative data analysis software environment, NVivo. NVivo will aid the coding of themes, organization, and searching of all interviews in both patient outcome categories (improvement vs worsening). The software will enable the comparison of themes across the full range of data (constant comparison, ie, comparing all bits of similar data with each other) [56] so more robust conclusions can be drawn.

While the researcher will drive the analysis, all investigators will be involved in group analytical sessions, debating and clarifying themes, and drafting of reports to arrive at the final analysis.

### Patient and Public Involvement

Patients were significantly involved in the design and piloting of the GES booklet before the trial started. Two patient representatives have also advised us in design of this trial and in the application and amendments to this trial. A patient representative is a member of the TMC, which will meet twice yearly. This individual will therefore be intimately involved in all aspects of this trial, so that we can ensure that this research reflects the needs and views of the patient group. A representative of the Association for Young People with ME will sit on the TSC.

### Ethics and Dissemination

The study was approved on November 23, 2011 (reference 11/LO/1572) by NRES Committee London, London Bridge. Four favorable opinions were provided on May 8, 2012, May 31, 2012, June 27, 2012, and June 20, 2013, for amendments to the study protocol and documents. A fifth amendment, requesting the addition of a nested qualitative study was rejected on 2014 September 1, with the suggestion it should be submitted as a separate study. The qualitative study received a favorable ethical opinion on January 9, 2015 (reference 15/WM/0007) by NRES Committee West Midlands, The Black Country. All patients involved in the study provided informed consent to take part in the study.

The results of the GETSET study will be disseminated to the scientific community, media, relevant charities, and general public. Results will be published in peer-reviewed international journals and will be presented at national and international conferences and symposiums.

## Results

The trial has finished recruiting (first randomization: May 15, 2013; last randomization: December 24, 2014). Follow-up for the main analysis was completed in April 2014 and long-term follow-up in March 2016. Data analysis are underway and the first results are expected to be submitted for publication later this year.

## Discussion

CFS/ME is a relatively common and frequently disabling condition with limited treatment options of proved efficacy available within the NHS. GET is recommended, but access to it is limited, with patients often spending many months waiting for rehabilitative therapy with no help given during that time. The longer someone has CFS/ME, the worse the prognosis [6].

Guided exercise self-help (GES) has never been tested in a randomized controlled trial for CFS/ME. It is important for people with CFS and the NHS to know whether GES is more effective, and cost-effective, when used with SMC, than when SMC is used alone.

If this trial shows GES to be acceptable and safe, and shows a clinically useful difference between arms, then the GES booklet will be made available on the Internet and through other media as a practitioner resource, with the knowledge that it is an acceptable, safe, and effective treatment when supported by advice from a trained therapist. If found to be cost-effective, then it could be recommended for commissioners of services. It could be used as a first line of treatment while patients are waiting for face-to-face specialist practitioner-delivered therapies, such as GET and CBT. Guided self-help exercise could become the first step in a stepped-care approach for CFS/ME in the NHS, by training current physiotherapists to deliver it.

The next trial would be to test this intervention in primary care, which could immediately follow this trial. The secondary care trial is necessary first, to ensure this intervention is effective in those with properly diagnosed CFS/ME, before testing it in those at the primary care level, where the diagnosis is not so well-established [57].

If shown to be an effective treatment, this policy of providing a guided self-help approach to initially stabilize and then increase PA in patients with CFS/ME could also be tested for patients with many other chronic disabling conditions known to respond to practitioner-delivered graded exercise approaches, including arthritis, chronic obstructive airways disease, and diabetes mellitus [58].

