#### Baseline

The following self-rated inventories will be collected at the first assessment (baseline): 11-item Chalder fatigue questionnaire (CFQ), using Likert scoring [30]; SF-36 physical function short form subscale (SF-36 PF) [31]; Hospital Anxiety and Depression Scale (HADS) [32]; Euroqol Questionnaire (EQ-5D) [33]; Work and Social Adjustment Scale (WSAS) [34]; International Physical Activity Questionnaire (IPAQ) [35]; Tampa Scale of Kinesiophobia-Fatigue (TSK-F) [36]; Client Service Receipt Inventory (CSRI) [37]; and Patient Health Questionnaire (PHQ-15) [38]. Participants will be asked when their CFS/ME started; whether they have ever received GET, CBT, or pacing from a therapist; whether they have ever used any listed self-help resources; and whether they are members of a CFS/ME self-help group. Participants will also be asked about their ethnicity, highest education level, current employment status, whether they have had to reduce/stop work due to their CFS/ME, other health problems, and whether they are taking antidepressant medication for any reason.

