#### Sample Size

Our original sample size was based upon the SF-36 PF as our primary outcome; however, the significance level was reduced to 2.5% to accommodate 2 primary outcomes [31]. A large previous trial of CFS/ME using the SF-36 PF (the PACE trial) indicated a baseline mean score of 37 (SD 15) and an outcome score of 48 (SD 21) following 12 weeks of practitioner-led GET, an 11-point increase [11]. Based on these previous findings, and our estimate that GES will be less effective than GET, the sample size calculations are based on the assumption that a mean difference of 8 (SD 18) points between intervention arms at the 12-week follow-up will be a clinically useful difference on the SF-36 PF scale after 12 weeks [11]. Thus, assuming a significance level (alpha) of 2.5% and power of 80%, we require a minimum of 98 participants in each group. This sample size will be upwardly adjusted to allow for loss to follow-up and other compliance issues. Based upon previous trials, we expect about 10% loss to trial follow-up [17]; therefore, we will recruit 109 patients in each group (a total of 218).

Based on a previous trial of GET, in which the difference between baseline and 12 weeks was 5.4 points on the CFQ [11], we assume that a mean difference of 3 (SD 6) points will represent a clinically useful difference at the 12-week follow-up. Hence, assuming a significance level (alpha) of 2.5% and power of 80%, we require a total of 174 patients, which is less than the 218 to be recruited, so adequate power will be achieved.

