#### Data Entry and Analysis

Data will be double entered by a dedicated data-entry researcher. The analysis and presentation of the trial will be in accordance with CONSORT guidelines including a flow diagram of enrollment, allocation, follow-up, and analysis [26,44]. We plan to use descriptive statistics to compare characteristics of invited individuals who did or did not agree to take part and eligible individuals who were randomized or not randomized (pending ethical approval). We will also examine differences between trial arms in important baseline participant characteristics.

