#### Missing Data

Item-level missing data on the primary and secondary outcome variables at baseline and follow-up will be imputed using mean replacement (prorating). Prorating will be implemented only when less than 20% of item responses per scale are missing. The reasons for missing baseline and follow-up whole-scale data will be summarized using the CONSORT diagram. We will identify baseline characteristics associated with missing data to allow us to impute data to do sensitivity analyses.

#### Analysis for Hypothesis 1

Our primary intention-to-treat analysis will compare the SF-36 PF and CFQ at 12 weeks between groups adjusted using multivariable linear regression analyses [45]. Intention-to-treat (ITT) analyses will be conducted on data from all randomized participants with information at follow-up (ie, modified ITT) regardless of any departure from the allocated treatment arm. We will adjust for our stratification factors (depression, center, and severity of disability) as well as baseline values of outcomes and treatment arm.

A secondary analysis will explore the association between treatment arm and having achieved a clinically useful improvement on the SF-36 PF (ie, an 8-point increase) and the CFQ (ie, a 3-point decrease) using chi-squared analysis.

Analysis of the secondary outcome, the CGI, will compare the proportions scoring “much” or “very much” better (1 and 2), the proportions scoring “a little better,” “no change,” or “a little worse” (3 to 5), and the proportions scoring “much” or “very much” worse (6 and 7) across treatment arms, using an ordinal logistic regression adjusting for our stratification variables.

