#### Sensitivity Analysis

Sensitivity analysis will be conducted to assess the impact of missing data on our results. We will estimate whole-scale missing data due to loss to follow-up using multiple imputation by chained equation. This will allow us to conduct a strict ITT for all respondents who took part at baseline. Following recent guidelines, we will also conduct a sensitivity analysis that will take into account the partially nested design of the study and, therefore, assess the potential impact of the “therapist effect” on our results [46]. Further analysis will be conducted to adjust for potential confounders, including sex and age.

A per-protocol analysis will serve as a further sensitivity analysis to investigate the robustness of the conclusions of the primary analysis, following departures from the randomized intervention policies. This will exclude those participants in the control arm who used a GET self-help approach. Subgroup analyses including only those meeting the Oxford or CDC criteria for CFS will also be undertaken. We will analyze moderators of improvement, such as these criteria, but also depression and severity of physical function and fatigue. These subgroup analyses are exploratory and will be interpreted with due caution [47].

#### Analysis for Hypotheses 2 and 3

Chi square will be used to describe any difference in satisfaction (ie, satisfied vs nonsatisfied) across treatment arms and any differences in SAEs, SARs, or serious deterioration (1+ vs none) across treatment arms.

The above plan is what we intend to do; however, the final analyses reported may differ from those planned, allowing for *post hoc* analysis where it is indicated [48]. We will report alternative methods if statistical models do not converge, and omit planned analyses that are superseded, redundant, or no longer of interest. We will report any changes in consequent papers.

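### Illness duration is called prognostic and can be derived from baseline data, but no adjusted analysis names it: a small missed gain in precision, not an error

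*Protocol article*

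**What the plan says.** Five places in the protocol article bear on this.

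- **Discussion.** In arguing that people wait months for therapy without help, the text says "The longer someone has CFS/ME, the worse the prognosis". It cites a source and gives no figure.
- **Baseline** (under Assessments and Procedures). "Participants will be asked when their CFS/ME started", so duration at entry can be derived.
- **Randomization.** The strata are depression, severity of disability and center. Duration is not one of them.
- **Analysis for Hypothesis 1.** The covariates of both primary regressions are listed: "We will adjust for our stratification factors (depression, center, and severity of disability) as well as baseline values of outcomes and treatment arm".
- **Sensitivity Analysis.** "Further analysis will be conducted to adjust for potential confounders, including sex and age". The wording leaves the list open, and duration is not named. It is not among the named moderators in that section either.

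Data Entry and Analysis adds: "We will also examine differences between trial arms in important baseline participant characteristics". This describes the arms and adjusts for nothing.

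**The concern.** The authors treat duration as related to outcome and collect what is needed to derive it, but none of the adjusted analyses names it. Duration may also vary widely. The NICE criteria were chosen partly because they require a shorter illness, and Inclusion/Exclusion Criteria states a minimum of just over 4 months and no maximum.

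Two things are at stake, both modest. The first is precision: whatever part of the 12-week scores duration predicts, beyond the planned covariates, stays in the residual variance. The second is credibility. If the baseline table shows the arms differing in duration, the plan names no response. An adjustment chosen after seeing an imbalance, in a trial with self-rated outcomes and participants who know their allocation, persuades less than one fixed beforehand.

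The covariate list for the primary regressions is stated in the article, so this is a comment on a choice made there and not on a detail left to an analysis plan.

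**Working it through.** **Inputs from Sample Size.** For SF-36 PF, "a mean difference of 8 (SD 18) points between intervention arms"; for the CFQ, "we assume that a mean difference of 3 (SD 6) points"; for each outcome, "assuming a significance level (alpha) of 2.5% and power of 80" percent; 98 evaluable per group; 10% loss; 218 recruited; 174 in total for the CFQ.

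**Assumed input.** The partial R² of duration, meaning the share of residual variance it explains once the planned covariates are in the model. The documents give no value. The main range is 1–5%, with 10% shown as an extreme.

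**Step 1: reproduce the plan's figures.** n per arm = 2 × [SD × (z₁₋α/₂ + z_power) / difference]².

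- SF-36 PF, two-sided 2.5%: 96.2, so 97 by the normal approximation. The noncentral t distribution gives 98, as stated. 98 / 0.9 = 108.9, so 109 per arm and 218 in total.
- CFQ: 76.0, so 77 by the normal approximation and 78 by the t distribution. 78 / 0.9 = 86.7, so 87 per arm and 174 in total.
- A one-sided 2.5% test would give 80 per arm for SF-36 PF, which does not match.

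The stated sizes therefore reproduce as two-sided tests on the full SD with no credit for any covariate. The planned power does not depend on duration.

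**Step 2: standard error.** Without duration, SE = 18 × √(2/98) = 2.571 points on SF-36 PF. With it, SE = 2.571 × √(1 − R²).

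- R² = 1%: 2.559, a fall of 1 − √0.99 = 0.5%.
- R² = 5%: 2.506, a fall of 1 − √0.95 = 2.5%.

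As a sample-size equivalent, 218 × [1/(1 − R²) − 1] gives 2.2 patients at 1% and 11.5 at 5%.

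**Step 3: power at 98 per arm, two-sided 2.5%, normal approximation.**

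| Partial R² (assumed) | SF-36 PF | CFQ |
|---|---|---|
| 0 (as planned) | 80.8% | 89.6% |
| 1% | 81.2% | 89.9% |
| 2% | 81.6% | 90.2% |
| 5% | 82.9% | 91.1% |
| 10% | 85.0% | 92.6% |

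**Step 4: allow for the planned covariates.** If these already explain 25% of outcome variance (also an assumption), SF-36 PF power is 91.2% without duration, and 91.5% and 92.6% at partial R² of 1% and 5%. The gain shrinks from 0.4–2.1 percentage points to 0.3–1.4. Separately, if the baseline score, disability stratum and depression already carry part of the duration effect, the partial R² itself will be lower.

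**The case against.** The strongest reply is that the prognostic sentence is background. It concerns the general course of the illness, and the Introduction cites the same source for recovery without treatment. Nothing in the article says that duration predicts 12-week SF-36 PF or CFQ scores given the baseline score, disability stratum, depression and center, and only that conditional association affects precision. This stands, and it is why every gain above is labelled as assumed.

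The second reply is that the planned model is sound. Each regression adjusts for the baseline value of its outcome, usually the strongest predictor of a repeated scale, and for all the stratification factors. This also stands.

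A reader might infer that omitting duration leaves the primary estimates exposed to distortion by chance imbalance. The documents do not support that. At 98 per arm, the standardized difference in duration has SD √(2/98) = 0.143, so 95% of trials fall within 1.96 × 0.143 = 0.28. Even at that limit the shift would be √R² × 18 × 0.28, or 0.5 points at R² = 1% and 1.1 at 5%. This describes a difference with no covariate adjustment, whereas the planned analysis is adjusted. It is also chance variation that the SE of 2.571 and the confidence interval already include, so it is not a second harm on top of the loss of precision.

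The third reply is that the further adjusted analysis has an open list and could take in duration. That is true, but it covers only a sensitivity analysis and leaves the selection to discretion.

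The fourth is timing. Results says that recruitment and follow-up are finished and that analysis is under way, so changing a primary model now needs care. This stands and shapes the fix.

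**Conclusion.** The point holds as a minor improvement. The article calls duration prognostic, records onset and names duration in neither the primary nor the further adjusted analysis. The treatment comparison is not biased by the omission, its type I error is correct and its stated power is unaffected.

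Under an assumed partial R² of 1–5%, the cost is a standard error 0.5–2.5% larger than it could be. That is about 0.4–2.1 percentage points of power on SF-36 PF and 0.3–1.5 on the CFQ (91.1 − 89.6 at the top), or less if the planned covariates already carry part of the effect. These figures rest on the assumed range, on the plan's own SDs and on 98 evaluable participants per arm. A reading that the primary analysis is flawed or unprotected goes further than the text allows.

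**What to change.** If the main analysis has not been done and the statistician is still masked, as Blinding to Outcome Measures intends, add illness duration at baseline to the covariates of both regressions in Analysis for Hypothesis 1. Derive it from the recorded onset and fix its form in advance. A log transformation is one reasonable choice, although the documents do not prescribe one. Report the model without duration as a sensitivity analysis.

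If allocation is already known, leave the primary models alone. Name duration beside sex and age in the further adjusted analysis under Sensitivity Analysis, and report this as a change from the plan, which the article already undertakes to do for any changes.

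The cost is one line of text, one degree of freedom per model and a simple rule for any missing onset dates. No new data are needed.
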